## Discussion

3

### Rationale for a multimodal approach

3.1

The primary objective of this study is to investigate the clinical efficacy of a combined repetitive transcranial magnetic stimulation (rTMS) and Chinese square dance intervention on cognitive function, neuroplasticity, and physical performance in older adults with mild cognitive impairment (MCI). A 2×2 factorial design is being used to disentangle the independent and combined contributions of these two modalities. The rationale is that iTBS-induced modulation of cortical excitability and DMI-induced upregulation of neurotrophic and cardiovascular pathways are hypothesized to converge on shared neurobiological mechanisms relevant to cognition in MCI (Cirillo et al., 2017). iTBS offers practical advantages (approximately 3-min sessions), and the combined protocol is hypothesized to capitalise on a potential priming effect, although this synergy remains to be tested empirically (Givralli et al., 2026).

### Insights from previous studies on behavioral symptoms and engagement

3.2

Apathy is a clinically meaningful target in MCI, as reduced motivation may limit participation in lifestyle interventions. iTBS over the left DLPFC has been reported to improve both global cognition and neuropsychiatric symptoms in MCI (Chu et al., 2021; Han et al., 2026). We hypothesize that, if present, rTMS-induced improvements in motivation and drive may support higher adherence to subsequent DMI sessions; this mediation effect will be interpreted cautiously given the sample size.

### Social engagement and cultural accessibility

3.3

The group-based, culturally familiar format of Chinese square dancing is hypothesized to address social isolation, a modifiable risk factor for cognitive decline (Read et al., 2020), by combining physical activity with structured social interaction. Observational data further suggest an association between long-term Chinese square dancing and preserved cognitive performance in older adults (Zhao et al., 2024); the present trial, however, is not designed to isolate the social contribution from the rTMS effect.

### Outcome measures and clinical relevance

3.4

The selected outcomes capture cognitive, physical, and behavioral dimensions most relevant to MCI. MoCA provides a measure of global cognition; BBS and 6MWT capture motor and cardiovascular function relevant to independence and fall risk. Qualitative interviews will contextualize feasibility and acceptability from participant and staff perspectives.

### The relationship between education level and intervention efficacy

3.5

Cognitive reserve, shaped by education, may modulate how older adults engage with combined cognitive-physical interventions. Because Chinese square dancing demands continuous attention, working memory, and spatial planning to synchronize complex movements with music, individuals with higher educational attainment may adapt more readily. We hypothesize that rTMS-induced modulation of cortical excitability may lower the cognitive threshold for learning these routines, potentially allowing adults with lower educational backgrounds to derive comparable benefits; this hypothesis will be tested in a pre-specified subgroup analysis.

### Adverse events and safety in the older adult population

3.6

rTMS-associated adverse events in older adults are typically mild and transient (Rossi et al., 2021). The DMI protocol includes heart-rate monitoring and a seated option to limit fatigue and fall risk.

### Ethics and dissemination

3.7

#### Ethical approval and conduct

3.7.1

This study protocol has been reviewed and formally approved by the Research Ethics Committee, Ethics Committee of Handan Central Hospital (Approval Number: (2026) Ethics Review Paper No. (078)). All trial procedures, including both the quantitative interventions and the qualitative interviews, will be conducted in strict adherence to the ethical principles outlined in the Declaration of Helsinki and all relevant national regulations governing human subject’s research.

#### Informed consent

3.7.2

Participation in this study is entirely voluntary. Prior to enrollment and any study-related procedures, all eligible participants—and their legally authorized representatives or family members, as appropriate—will receive comprehensive information regarding the study’s objectives, the nature of the interventions (rTMS and Chinese square dancing), potential risks, and expected benefits. Written informed consent will be obtained from all participants for the main randomized controlled trial. Furthermore, participants purposively selected for the embedded qualitative component will be required to provide an additional, specific written informed consent prior to participating in the interviews and being audio-recorded.

#### Right to withdraw

3.7.3

Participants will be explicitly informed of their right to withdraw their consent and discontinue participation in either the main trial, the qualitative interview, or both, at any time. They will be assured that withdrawal can be done without providing a reason and will not result in any adverse consequences to their ongoing medical care, treatment, or relationship with Handan Central Hospital.

#### Data confidentiality and security

3.7.4

Strict protocols will be implemented to safeguard participant privacy and data confidentiality. All collected clinical data, demographic information, and qualitative transcripts will be completely de-identified and assigned a unique, randomized study code. Original paper consent forms and physical assessment records will be stored in a locked filing cabinet within a restricted-access research office. All electronic data, including coded databases and audio recordings, will be encrypted and stored on secure, password-protected hospital servers. Access to any identifying information will be strictly limited to the principal investigator and the core research team. Following the completion of the study and publication of the results, all data will be securely retained for a minimum of five years before being permanently destroyed in accordance with institutional data governance policies.

#### Safety monitoring and serious adverse event reporting protocol

3.7.5

An Adverse Event (AE) is defined as any untoward medical occurrence in a participant during the study, regardless of its causal relationship with the intervention. Expected, mild AEs (e.g., transient scalp discomfort from iTBS, mild delayed-onset muscle soreness from the DMI) will be managed conservatively by the supervising medical staff and documented in the participant’s case report form (CRF).

A Serious Adverse Event (SAE) is strictly defined as any event that results in death, is life-threatening, requires inpatient hospitalization, or results in persistent or significant disability/incapacity. In the event of an SAE, a rapid-response reporting protocol will be initiated. The supervising trial instructor must notify the Principal Investigator immediately (within 24 hours of awareness). The Principal Investigator is then legally and ethically mandated to formally submit a detailed SAE report to the Medical Ethics Committee of Handan Central Hospital within 48 hours. Furthermore, the trial steering committee will evaluate the SAE to determine if trial protocols require modification or suspension, and the event will be officially updated and disclosed on the Chinese Clinical Trial Registry in accordance with international trial transparency guidelines.

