### Participants

2.2

Participants will be recruited from the Department of Rehabilitation at Handan Central Hospital. A convenience sampling method will be employed, with local physicians providing a list of potentially eligible patients diagnosed with MCI. All participants will provide written informed consent before enrollment. A family member or legal guardian will also be asked to co-sign the consent form. Participant data will be anonymized to ensure confidentiality. The data will be secured during the study and destroyed five years after the study completion.

Inclusion criteria: (1) Diagnosis of amnestic or multi-domain MCI by a specialist physician according to the National Institute on Aging-Alzheimer’s Association (NIA-AA) criteria. (2) Age between 50 and 85 years. (3) Montreal Cognitive Assessment (MoCA) score between 18 and 25. (4) Geriatric Depression Scale (GDS-15) score < 5. (5) Physically able to participate in dance activities without assistive devices and deemed at low risk for falls (Berg Balance Scale score ≥ 41). (6) Stable doses of any prescribed medications for at least 30 days prior to screening. (7) Sufficient visual and auditory acuity (with correction if necessary) to complete assessments and interventions. (8) Voluntarily agrees to participate and provides informed consent.

Exclusion criteria: (1) Diagnosis of dementia (any type). (2) Presence of major psychiatric conditions (e.g., major depressive disorder, schizophrenia) or neurological disorders (e.g., Parkinson’s disease, stroke) that could confound cognitive assessment. (3) Contraindications to rTMS (e.g., history of seizures, metallic implants in the head). (4) Regular participation in structured exercise (≥ 3 times per week) or another cognitive intervention program within the past six months. (5) Abuse of drugs or alcohol that could cause cognitive impairment.

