The study would cease if any of the following occurs: (1) Participant’s death. (2) Medical problems related to exercises (fracture, cardiac or cardiopulmonary problems, etc.). (3) Participants experience adverse event(s) that require discontinuation in the judgment of the principal investigator or trial instructor. (4) Participants have a need for additional intervention (such as cognitive treatment) that would interfere with the trial. (5) Participant neglects to follow trial instructions. (6) Participant have lost more than six sessions and cannot make additional lessons to cover the deficiency. (7) Participants or their legally authorized representative request consent withdrawal. An adverse event will be defined as any untoward medical occurrence in a participant during participation in the study. Adverse events include unbearable discomfort with rTMS intervention, falling, tripping, serious muscle soreness during dance participation. Participants will be allowed to finish all dance classes in a sitting position to prevent further adverse events if necessary.

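### The closed SAE definition in section 3.7.5 leaves out some exercise-related fractures and cardiac problems that section 2.2 treats as grounds to end participation, so these events have no required escalation

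*Protocol article*

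**What the plan says.** Section 3.7.5 (Safety monitoring and serious adverse event reporting protocol) defines an adverse event broadly, as any untoward medical occurrence whatever its cause. It then describes handling for two classes.

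- **Expected, mild events** (transient scalp discomfort and mild muscle soreness are the examples) "will be managed conservatively by the supervising medical staff and documented in the" case report form.
- **SAEs** are defined by a closed list: "A Serious Adverse Event (SAE) is strictly defined as any event that results in death, is life-threatening, requires inpatient hospitalization". Lasting or significant disability or incapacity is the fourth and last outcome on that list. The escalation steps open with "In the event of an SAE, a rapid-response reporting protocol will be initiated". The first step is "The supervising trial instructor must notify the Principal Investigator immediately (within 24 hours of awareness". An ethics report within 48 hours, steering-committee evaluation for possible modification or suspension, and registry disclosure follow.

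Section 2.2 (Participants) lists seven grounds for stopping. The second is "Medical problems related to exercises (fracture, cardiac or cardiopulmonary problems, etc". The third covers "adverse event(s) that require discontinuation in the judgment of the principal investigator or trial instructor". Neither depends on admission to hospital or on the event being an SAE.

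Adverse events are also captured in the instructor's session log for dance classes (section 2.3.2) and by the monitoring row of Table 1, which is marked for Weeks 1–12 and T1. Neither place states onward reporting.

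**The concern.** The article has two lists of important safety events, and they do not line up. One decides whether a participant stops. The other decides whether anyone beyond the session staff must be told. A fracture or cardiac problem can be on the first list and off the second.

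At stake is oversight while the trial runs. The steering-committee evaluation in section 3.7.5 is the only review described that can lead to modification or suspension, and its trigger is an SAE. If several dance participants stopped because of fractures treated as outpatients, staff could follow the article exactly and no committee would have to look at the pattern.

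**Working it through.** No figure in the plan needs reproducing; the check is a comparison of texts. I read the section 2.2 stopping grounds as applying to the individual participant, since most of them (missed sessions, withdrawn consent) make sense only that way.

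**Step 1. Is the SAE list closed?** Yes. The article calls it strict and gives four outcomes: death, threat to life, inpatient hospitalization, and persistent or significant disability or incapacity. It has no criterion for other events judged medically important.

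**Step 2. What depends on it?** Four steps: notice to the principal investigator (24 hours), the ethics report (48 hours), steering-committee evaluation, and registry disclosure. The stated trigger for all four is an SAE.

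**Step 3. Take an event under the second stopping ground.** Suppose an exercise-related fracture, or a cardiac problem that ends the class, is managed without admission, is not life-threatening and leaves no persistent or significant disability.

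| Test | Result |
|---|---|
| Second stopping ground, section 2.2 | Met |
| Death | Not met |
| Life-threatening | Not met |
| Inpatient hospitalization | Not met |
| Persistent or significant disability or incapacity | Not met |
| Expected, mild class | Does not fit |
| Captured as an adverse event (dance log, Table 1 monitoring) | Yes |
| Required escalation steps | 0 of 4 |

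**Step 4. Can the principal investigator learn of it another way?** Possibly. The third stopping ground names the principal investigator as a judge of discontinuation, but as an alternative to the trial instructor. The text allows the principal investigator to be involved without requiring it.

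**Step 5. Exposure, for context only.** The two dance arms have 40 + 40 = 80 participants, each with 3 × 12 = 36 scheduled classes, so 80 × 36 = 2,880 participant-sessions. This shows where exercise-related events would mostly arise. It does not measure the gap, because no event rates are given.

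**The case against.** The strongest reply is that stopping grounds and seriousness are different concepts. Section 2.2 also stops people for not following instructions or withdrawing consent, so a ground that is not an SAE is no error in itself. That is right, and I do not call the sections a formal contradiction. What stands is the effect of the closed definition on the two kinds of medical event that the second ground names.

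A second reply is that a journal article condenses, so handling of moderate, non-serious events may sit in the full protocol. Taken alone, a missing middle tier would indeed be weak ground. But the article sets out the SAE definition, trigger, deadlines and recipients, and a fuller document could not widen a definition described as strict without conflicting with it.

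Third, the disability criterion may capture some fractures in older adults. That narrows the gap but does not close it.

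Several stronger readings are tempting and are not supported:

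- **Seizure as a named stopping ground.** It appears only as a history that excludes entry: "Contraindications to rTMS (e.g., history of seizures, metallic implants in the head". A seizure during the trial could come under the general third ground, or be an SAE if judged life-threatening.
- **Non-serious events reach nobody.** They are captured by the dance log and the scheduled monitoring; what is missing is a required onward report.
- **The instructor has no role in stimulation sessions.** Section 2.3, which introduces both modalities, puts participants under the supervision of instructors and medical staff.
- **The final safety report will understate harm.** Nothing limits that report to SAEs, and adverse events are defined broadly and collected.

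**Conclusion.** The point holds in a limited form. As written, an exercise-related fracture or cardiac or cardiopulmonary problem can end participation yet require none of the four escalation steps. This rests on three conditions about the event: no admission, no threat to life, and no persistent or significant disability. Whether a given case meets them is a clinical judgment.

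The consequence is for oversight during the trial: such events could recur without the one described review that can modify or suspend it. How often is unknown, because the documents give no rates. The efficacy analysis is not affected. This is a cheap and worthwhile improvement to a stated rule, not evidence that harms will go unrecorded.

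**What to change.** Reconcile sections 2.2 and 3.7.5:

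1. Remove the wording in section 3.7.5 that closes the SAE definition.
2. Extend its reporting route to events meeting the second stopping ground of section 2.2, and to other events judged medically important, whether or not the participant is admitted.
3. Let any staff member who becomes aware of such an event make the report, instead of naming only the supervising trial instructor.

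Not every discontinuation under the third ground should go down this route. Section 2.2 counts unbearable discomfort with stimulation as an adverse event, so a tolerability dropout would then need an ethics report within 48 hours and steering-committee review. Who decides on discontinuation, and on what grounds, stays with the sponsor.

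The cost is a few sentences in the protocol, a matching change to the reporting form, and a few more expedited reports. No visits, staff or procedures are added.

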#### Dissemination

3.7.6

The findings of this trial will be disseminated through multiple channels to maximize their scientific and clinical impact. The primary results, encompassing both the quantitative efficacy outcomes and the qualitative findings from the embedded interview component, will be submitted for publication in a peer-reviewed, open-access journal. Interim and final results will also be presented at relevant national and international academic conferences in the fields of neurology, cognitive rehabilitation, and geriatric medicine.

In accordance with international clinical trial transparency guidelines, the trial registry record (ChiCTR2600127655) will be updated with summary results within 12 months of study completion. A lay summary of the findings will be provided to all participants upon request. Authorship of all publications arising from this study will adhere to the criteria established by the International Committee of Medical Journal Editors (ICMJE). No professional medical writers will be employed without full disclosure in the acknowledgements section.

## Conclusions

4

We hypothesize that the combined rTMS and DMI group will demonstrate superior and more durable improvements in global cognition and physical performance compared to the monotherapy or control groups. By providing a comprehensive, mixed-methods evaluation of this synergistic approach, this trial aims to inform future clinical guidelines and offer a feasible, culturally appropriate strategy for managing MCI in the aging population.

## Data Availability

Publicly available datasets were analyzed in this study. This data can be found here: This is a study protocol, the data is not available currently.

## Glossary

AD: Alzheimer’s disease
AE: Adverse Event
ANOVA: Analysis of Variance
BBI: Bang’s Blinding Index
BBS: Berg Balance Scale
BDNF: Brain-Derived Neurotrophic Factor
ChiCTR: Chinese Clinical Trial Registry
CONSORT: Consolidated Standards of Reporting Trials
COREQ: Consolidated Criteria for Reporting Qualitative Research
CRF: Case Report Form
DLPFC: Dorsolateral Prefrontal Cortex
DMN: Default Mode Network
DMI: Dance movement intervention
EEG: Electroencephalography
ERP: Event-Related Potential
FDR: False Discovery Rate
GDS-15: 15-item Geriatric Depression Scale
ICMJE: International Committee of Medical Journal Editors
IGF-1: Insulin-like Growth Factor 1
IQR: Interquartile Range
ITT: Intention-to-Treat
iTBS: Intermittent Theta Burst Stimulation
LMM: Linear Mixed-Effects Model
LTP: Long-Term Potentiation
MAR: Missing at Random
MCID: Minimal Clinically Important Difference
MCI: Mild cognitive impairment
MI: Multiple Imputation
MMSE: Mini-Mental State Examination
MoCA: Montreal Cognitive Assessment
NIA-AA: National Institute on Aging-Alzheimer’s Association
P300: P300 Event-Related Potential
RCT: Randomized Controlled Trial
rMT: Resting Motor Threshold
rs-fMRI: Resting-State Functional Magnetic Resonance Imaging
rTMS: Repetitive transcranial magnetic stimulation
SAE: Serious Adverse Event
SD: Standard Deviation
SF-12: 12-item Short Form Health Survey
SOP: Standard Operating Procedure
SPIRIT: Standard Protocol Items, Recommendations for Interventional Trials
TMT: Trail Making Test
6MWT: 6-Minute Walk Test
WMS-IV: Wechsler Memory Scale, Fourth Edition
